**Introduction**

Initial warnings that all countries would suffer SARS-Cov-2 (Covid-19) pandemic in 2020 have come true. With mean incubation period reported around 6 to 7 days, the disease is characterized by fever, sore throat, dyspnea, loss of smell and taste that could progress to irreversible damage to lungs leading to death. The global fatality rate of 3 – 4% has been estimated. In the continued absence of a definitive treatment or vaccine, this pandemic continues to harm public health, lifestyles, and economies around the world.

Hydroxychloroquine Sulphate (HQ), commonly used against malaria and rheumatoid arthritis in Indo-Asian region, was reported to stop symptomatic progression of SARS-Cov-2 by inhibiting pH dependent steps of viral replication. It’s effectiveness as monotherapy or in combination with common antibiotics and antivirals is being evaluated around the world. Non-randomized study of Guatret et al promoted the use of macrolides like Azithromycin with HQ in clearing the virus at day 6 among hospitalized patients. None of the 21 patients enrolled in this study reported any adverse drug reactions. Recruitment in HQ arm of ongoing Solidarity Trial resumed after initial concerns of cardiotoxicity were addresses by data safety review. To date, several countries have seen widespread compassionate use of HQ and Azithromycin during the ongoing pandemic.

*6b Explanation for choice of comparators*

Ulrich and Pillat have attributed interest in common antibiotic Azithromycin (Macrolide) to its mechanism of action against rhinovirus - interference with ligand/CD147 receptor interactions and decrease expression of some metalloproteinases (downstream to CD147) that inhibit viral replication. Oseltamivir was one of the earliest drugs tested on SARS-CoV-2 patients in Wuhan, China. With proven effectiveness against influenza viruses, it was evaluated as monotherapy and in combinations to rule out sharing of the same neuraminidase enzyme by novel Coronavirus.

***SPIRIT Guidance:*** *Objectives*

*7 Specific objectives or hypotheses*

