***2.1 Secondary Objectives***

- To evaluate various clinical parameters, quality of life, and symptoms scores, within all randomized participants stratified by subgroups
- To follow up participants not consenting to randomization for the outcomes of SARS-Cov-2 infection with supportive treatment only

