***Inclusion Criteria***

1. Confirmed SARS-CoV-2 (COVID-19) infection by a positive test result
2. Either gender
3. Symptomatic for example fever, dry cough, myalgias

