Secondary outcomes like Quality of Life and Symptoms Score will be recorded on day 0 and 7 using standardized tools such as World Health Organization Quality of Life Questionnaire (WHO QoL) and Wisconsin Upper Respiratory Symptoms Survey (WURSS) respectively (copies **attached)**. The former is expected to capture participant’s lived experience during care that has not been documented in literature to date. The latter is expected to indicate any respiratory co-infection including those acquired from the hospital. The investigators will also monitor and record variables including duration it takes to oxygenate and ventilate, duration stayed oxygenated and ventilate, number of hospitals stay days, admission to intensive care, and mortality. This methodology has been peer reviewed by an external expert **(see annex 1).** A GCP certified, experienced researcher will conduct the training of up to 50 investigators across 13 participating sites to prepare them for all aspects of this study.

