***SPIRIT Guidance: Ancillary and post-trial care***

30 Provisions, if any, for ancillary and post-trial care, and for compensation to those who suffer harm from trial participation

The study is conducted in view of lack of treatment options for mild to moderately symptomatic SARS-Cov-2 with a commitment to no-harm practices and a robust adverse drug reaction monitoring framework.

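### The protocol says the WURSS symptom score will indicate respiratory co-infection, but in participants enrolled with symptomatic COVID-19 the score cannot separate a second infection from COVID-19 itself

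*Protocol*

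**What the plan says.** The protocol's section on outcomes (SPIRIT item 12) names two secondary instruments, a WHO quality-of-life questionnaire and the WURSS, the latter serving as the symptoms score. On timing it says: "Secondary outcomes like Quality of Life and Symptoms Score will be recorded on day 0 and 7". On what the WURSS is for, it gives one statement only: "The latter is expected to indicate any respiratory co-infection including those acquired from the hospital".

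Four other places bear on that statement:

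- Inclusion Criteria, item 1: "Confirmed SARS-CoV-2 (COVID-19) infection by a positive test result".
- Inclusion Criteria, item 3: "Symptomatic for example fever, dry cough, myalgias".
- Introduction, describing COVID-19: "the disease is characterized by fever, sore throat, dyspnea, loss of smell and taste".
- Section 2.1, Secondary Objectives: "To evaluate various clinical parameters, quality of life, and symptoms scores, within all randomized participants stratified by subgroups".

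The section on statistical methods lists multiple regression, chi-square, Fisher's exact test and one-way ANOVA for secondary analyses, without saying which applies to the WURSS. Covariates are to come from the stratification factors, and only if baseline imbalance is seen.

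**The concern.** A symptom survey measures how ill a person feels and in what way. It does not identify the cause. In a population selected for having one symptomatic respiratory infection, the score will reflect that infection first, and the protocol nevertheless says it will point to a different one.

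What is at stake is how a secondary result is interpreted. Four of the seven arms contain azithromycin (alone, in two pairs, and in the triple regimen), which the protocol calls an antibiotic. By the same count, four contain oseltamivir, which it describes as effective against influenza. If symptoms settled faster in some arms, the protocol's sentence would invite the explanation that a bacterial or influenza co-infection had been prevented, when faster recovery from COVID-19 would produce the same scores. Neither physicians nor participants are blinded, which makes a self-reported score a still weaker basis for inferring infection.

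**Working it through.** The plan gives no figure on this point, so there is none to reproduce. The check is whether any score pattern, given what the protocol collects, could distinguish a co-infection from COVID-19.

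**Step 1: who is scored.** Inclusion items 1 and 3 together mean that participants have confirmed COVID-19 and are symptomatic. The section on post-trial care agrees, giving as the reason for the study the "lack of treatment options for mild to moderately symptomatic SARS-Cov-2". The narrative eligibility text in section 4 does not repeat the symptom criterion. If it were not enforced, the overlap would still affect every participant who has symptoms.

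**Step 2: do the symptoms overlap?** The protocol's own lists for COVID-19 include fever, dry cough, sore throat and dyspnoea. An upper respiratory symptom survey can be expected to register at least some of these. The attached copy of the instrument is not available here, so the individual items were not checked.

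**Step 3: what the two time points can show.**

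| Pattern | Explanation by COVID-19 alone | Explanation by co-infection |
|---|---|---|
| High on day 0 | Presenting illness, required for entry | Possible |
| Still high on day 7 | Unresolved illness | Possible |
| Higher on day 7 than on day 0 | Progression | Possible |

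Every pattern has both explanations.

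**Step 4: is there anything else to separate them?** The only virological test named in the outcomes section is qRT-PCR for SARS-CoV-2. Combining it with the WURSS does not help: the protocol treats viral clearance and clinical improvement as two distinct primary outcomes, so a negative swab does not establish that remaining symptoms have another cause.

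**Step 5: can the size of the error be stated?** Let p be the share of participants with a true co-infection, s the probability that they score positive, and f the probability that a participant with COVID-19 alone scores positive. The share of positive scores that are true is

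PPV = s·p / (s·p + f·(1 − p)).

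The document gives none of p, s or f, nor what counts as positive. With p assumed between 3% and 20%:

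| Assumed f | Assumed s | PPV at p = 3% | PPV at p = 20% |
|---|---|---|---|
| 1.0 | 1.0 | 3% | 20% |
| 0.5 | 0.9 | 0.027/(0.027 + 0.485) = 5% | 0.18/(0.18 + 0.40) = 31% |
| 0.2 | 0.9 | 0.027/(0.027 + 0.194) = 12% | 0.18/(0.18 + 0.16) = 53% |
| 0.1 | 0.9 | 0.027/(0.027 + 0.097) = 22% | 0.18/(0.18 + 0.08) = 69% |

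The result runs from 3% to 69% depending on what is assumed. The table shows that no single figure can be given. It does not estimate the error in this trial.

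**The case against.** The strongest reply is that the sentence is rationale and not method. It parallels the preceding sentence about quality of life, and the SPIRIT item printed above it asks for an explanation of clinical relevance. It sets no cut-off and classifies nobody. Co-infection appears in no objective, and the statistical section names no co-infection analysis. The secondary objective concerns symptom scores as such, and the comparison of scores between arms is valid whatever the sentence says. Scoring details may also stand in an analysis plan that is not shown.

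Most of this stands, and it limits the point. A reader might infer that the protocol contains a rule flagging COVID-19 patients as co-infected, and that a difference in scores would be reported as a difference in co-infection. The text supports neither. A reader might also work out that a stated majority of indications would be false, but any such figure depends on assumed frequencies and on a positivity rule that the protocol does not contain. Nor can it be said that home-isolated participants could not acquire a hospital infection: the recruitment section has them identified by investigators in the hospital, so exposure there is possible.

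The reply does not rescue the sentence itself. It is the only meaning the protocol gives this outcome, and it stands where outcomes are defined. An analysis plan could add a threshold or a change criterion, but neither would make a symptom total specific to a pathogen.

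**Conclusion.** The point holds as an unsupported interpretation of one secondary outcome. Given the entry criteria, the protocol's own description of COVID-19 and the absence of any named test for another pathogen, no WURSS pattern on days 0 and 7 can be attributed to co-infection. The conclusion assumes that inclusion item 3 is applied as written and that the survey covers at least some of the symptoms the protocol lists for COVID-19.

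The effect is on reporting only. The WURSS remains usable as a measure of symptom severity. The change is worth making but should not hold up the trial.

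**What to change.** 1. Delete the sentence on co-infection from the outcomes section.
2. Replace it with wording such as: *The WURSS is a symptom-severity outcome. The day-7 score will be compared between randomised groups with the day-0 score as covariate.* This matches section 2.1 and uses both scores already collected. It is preferable to an unadjusted one-way ANOVA, and the day-0 adjustment should be fixed in advance, not made conditional on observed imbalance. The day-0 score should be the one taken before the first dose.
3. Draw no conclusion about co-infection from the WURSS. If diagnoses recorded by site physicians are reported, present them descriptively for all randomised participants. State that physicians knew the allocation and that diagnostic facilities differ between sites. Restricting the count to admitted participants should be avoided, because admission can occur after randomisation and may depend on the treatment received.

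The cost is a few lines of protocol text and a matching line in the analysis plan. No new data, visit or test is needed. The trial gives up any claim about co-infection based on symptoms, which the data could not have supported.

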***SPIRIT Guidance: Participant timeline***

*13 Time schedules of enrolment, interventions (including any run-ins and washouts), assessments, and visits for participants. A schematic diagram is highly recommended (see Figure)*

Flow Chart **(Figure 1)**

***SPIRIT Guidance: Sample size***

*14 Estimated number of participants needed to achieve study objectives and how it was determined, including clinical and statistical assumptions supporting any sample size calculations*

This is an adaptive design and parameters for formal sample size calculation in a new disease of a previously unknown virus are not available. Then the sample size and power analysis are indicative for review at each stage of adaptive design. In a standard two-arm, head-to-head trial, the sample size would have been as follows: in order to detect a difference in the laboratory-based primary outcome of 10% (assuming a 50% of participants receiving Hydroxychloroquine Phosphate/Sulfate turn test negative at day 7 and expected rates in comparator groups of 60%), at a significance level 5% and a power of 90%, a sample size of approximately 520 subjects in each group will be required. This sample size will be enough to detect a small-medium difference (Cohen’s d 0.3, a significance level 5% and a power of 90%) in the clinical primary outcome. Additional considerations will need to make for the interim analysis at every stage of the adaptive design. Interim analysis will review sample size according to time to clearance also. Planned blinded sample size re-estimations will need to be undertaken in which we will constantly re-examine the original sample size assumptions. We will aim to maintain the trial power at 90% even if the original sample size assumptions turn out to be far from the observed data. The adaptation at each stage will allow us to drop out fewer promising interventions and will prevent an underpowered trial for the most promising interventions. As the planned modifications will be undertaken in a blinded fashion, there will be no increase in the type I error rate.

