***SPIRIT Guidance: Statistical methods***

*20a Statistical methods for analyzing primary and secondary outcomes. Reference to where other details of the statistical analysis plan can be found, if not in the protocol*

*20b Methods for any additional analyses (eg, subgroup and adjusted analyses)*

*20c Definition of analysis population relating to protocol non-adherence (eg, as randomized analysis), and any statistical methods to handle missing data (eg, multiple imputation)*

All trial data will be analyzed by biostatistician based at the University of Health Sciences, Lahore, using an a priori, approved analysis plan (SPSS 25.0). Interim analyses at each stage (first stage will be 10% of the total sample size) of the adaptive design will be pre-planned and undertaken confidentially keeping investigators and participants blind till the end of the trial. Primary and secondary outcomes will be analyzed in accordance to the group in which the participants were randomized deploying the intention-to-treat principle. The primary analysis will be expressed as odds ratio (OR) of the comparison between groups for the primary outcome. Interim analyses will be conducted without disclosing groups, thereby maintaining a level of blinding in interpretation of interim results. The confidential interim analyses at each stage of the adaptive design will examine for imbalance in co-morbidity at baseline. If any differences are observed then stratification may be modified confidentially. The results will be reported as point estimates and 95% confidence intervals. Secondary analysis will include in time-to-event data to directly compare the data among groups with survival plots and hazard ratios. This will permit evaluation of the decision to continue beyond Day 7 of treatment upon testing negative, potential drug effects besides informing valuable understanding of drug effectiveness. Stratified analyses will be done by baseline COVID-19 positive status upon testing and age groups. Multiple regression and Cox proportional hazards stratified analysis will be used to adjust for a small number of covariates taken from stratification factors if there were baseline imbalances. Secondary analyses will deploy multiple regression models as well Chi square, Fisher’s exact test and one-way ANOVA to compare groups. The two-sided p-value less than or equal to 0.05 will be taken as significant. Imputation method will be used to handle missing data.

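### The assurance that blinded adaptations cannot raise the type I error holds for pooled sample size re-estimation but not for dropping arms, so the 5% level is not assured

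*Protocol*

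**What the plan says.** Protocol, SPIRIT item 14 (Sample size), describes two adaptations. The first is blinded re-estimation of the sample size, meant to keep power at its target. The second is selection among arms: "The adaptation at each stage will allow us to drop out fewer promising interventions", which in context means dropping the less promising ones. The section then closes with one sentence covering both: "As the planned modifications will be undertaken in a blinded fashion, there will be no increase in the type I error rate". Shortly before, it says that further allowance will be needed for the interim analysis at each stage, without saying what.

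SPIRIT item 20 (Statistical methods) shows what blinding means here: "Interim analyses will be conducted without disclosing groups, thereby maintaining a level of blinding in interpretation of interim results". Investigators and participants are also kept from the results. On timing it gives only the first look: "Interim analyses at each stage (first stage will be 10% of the total sample size". The number and timing of later stages are not given. The significance criterion is: "The two-sided p-value less than or equal to 0.05 will be taken as significant".

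Section 8 gives the national monitoring board (NDSMB) authority to halt an arm. SPIRIT item 21b assigns the interim analyses to an independent NDSMB sub-committee that includes the study statistician.

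**The concern.** Blinding protects the type I error when the adaptation uses no information about the treatment contrast. Re-estimating the sample size from the pooled event rate meets that condition. Arm dropping cannot, because ranking arms requires a comparison of their outcomes. Coded labels limit operational bias, but the choice of arm still depends on the observed differences.

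The inference in the closing sentence therefore fails for one of the two adaptations it covers. If a selected arm is then tested at an unadjusted 0.05, a positive result would be reported at 5% although its false-positive rate can be higher. The sentence also gives whoever writes the detailed analysis plan a reason to make no adjustment.

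**Working it through.** **Inputs from the protocol.** Rates 50% (HCQ) and 60% (comparators), 5% level, 90% power, about 520 per group for one two-arm comparison (item 14); seven randomised arms (item 11a); first stage at 10% (item 20); two-sided p ≤ 0.05 (item 20).

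**Assumptions.** Equal allocation, HCQ alone as the reference (hence six comparisons), and the selection rules named below. The protocol states none of these.

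**1. The plan's own figure.**
n = [z(0.975)·√(2·0.55·0.45) + z(0.90)·√(0.5·0.5 + 0.6·0.4)]² / 0.1²
= (1.960·0.7036 + 1.2816·0.7000)² / 0.01
= (1.3790 + 0.8971)² / 0.01 ≈ 518, or 519 when rounding is done upwards.
The stated 520 is reproduced, for one comparison with no interim look.

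**2. Pooled re-estimation.** Simulation under the null (200,000 runs, one pair, pooled rate read at 260 per arm) gives 5.2%, against 5.0% to 5.1% for the same test without adaptation. The sentence is sound for this adaptation.

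**3. Best of six kept, then tested once against HCQ at an unadjusted 0.05.** With all arms equal, seven normal arm means are simulated at information fraction f, the best comparator is kept, and the final statistic is (kept arm − HCQ)/√2 (1,000,000 runs):

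| Selection at | Two-sided error (nominal 5%) | Favourable direction (nominal 2.5%) |
|---|---|---|
| 10% | 5.6% | 4.5% |
| 25% | 6.5% | 5.8% |
| 50% | 7.9% | 7.6% |

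Binomial simulation at 520 per arm agrees to within about 0.2 points (5.7%, 6.5%, 8.0% two-sided).

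**4. Lagging arm dropped, with no early efficacy claim and one fixed pair.** Under the null, reversing the sign of both the interim and the final statistic leaves their joint distribution unchanged. Hence P(ahead at interim and |Z| > 1.96) = 5%/2 = 2.5%. Binomial simulation gives 2.5% to 2.7%, the excess arising because ties are kept. There is no inflation.

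**5. Family of comparisons.** Six unadjusted comparisons with HCQ and no dropping give a familywise error of about 21%. Keeping the best three of six gives 12.6% (selection at 10%) to 11.8% (at 50%). Dropping lowers the familywise error, but it stays above 5%.

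**6. Only if efficacy were also tested at 0.05 at each look.** One pair would reach about 9.5% (looks at 10% and 100%), 12.3% (10%, 50%, 100%) or 19% (ten equal looks). Binomial counts give up to about one point more.

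**7. Price of a family-wide critical value.** Dunnett over six comparisons has critical value about 2.567, that is p ≤ 0.0103 for each.
Power at 520 = Φ[(0.1 − 2.567·√(0.495/520)) / √(0.49/520)] = Φ[(0.1 − 0.0792)/0.0307] = Φ(0.68) ≈ 75%.
For 90%: n = (2.567·0.7036 + 0.8971)²/0.01 ≈ 731 per arm.

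**The case against.** The strongest reply is that dropping arms is not harmful to the type I error in itself. Step 4 shows that a fixed pairwise comparison becomes conservative, and step 5 that the familywise error falls. This stands. A reader might infer that the 5% level is definitely broken by the design, and the documents do not support that: the dropping rule, the reference arm and the error rate to be controlled are not stated. Most of the familywise excess also comes from the number of unadjusted comparisons rather than from dropping.

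A reader might also infer that 0.05 is applied at every stage, and so quote 9.5% to 19% as the trial's error rate. The protocol neither says nor excludes this. The stage purposes it names are sample size review, dropping arms and checking baseline co-morbidity, and the 0.05 sentence follows the list of secondary analyses without mentioning interim looks.

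Finally, boundaries and multiplicity adjustments are commonly left to an analysis plan, and item 20 refers to one that is not shown. Their absence is therefore no finding. The monitoring board and its sub-committee already provide the right body to see outcomes by arm.

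None of this rescues the sentence itself. It is an affirmative statement in the protocol, resting on a reason that does not apply to arm dropping.

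**Conclusion.** The assurance of no type I error increase is valid for blinded pooled-data re-estimation and wrong for arm dropping. The 5% level is therefore not assured, although it is not shown to be broken.

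Under the illustrative best-of-six rule the error is 5.6% (selection at 10%, the only stage the protocol fixes) to 7.9% (at 50%, an assumed timing). In the favourable direction it is 4.5% to 7.6% against 2.5%. These figures assume that one arm is kept, that HCQ alone is the reference, and that there is a single unadjusted final test. With lagging arms dropped, no early claims and a fixed pair, there is no excess.

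**What to change.** - **Item 14.** Limit the sentence to sample size re-estimation from pooled data. Say that dropping arms is a comparative analysis, done by the independent NDSMB sub-committee, and who sees outcomes by arm.
- **Role of the stage analyses.** State that they are for lack of benefit only, with no efficacy claim unless a pre-specified alpha-spending boundary is crossed.
- **Final test.** State which error rate it controls. If a selected arm or the family of comparisons is to be claimed at 5%, use a critical value that accounts for every arm that started, not only those that remain.

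The wording costs little, but the critical value may not. The protocol intends to hold power at 90%. With a Dunnett-type value over six comparisons with HCQ, power at 520 per arm is about 75%. Restoring 90% needs about 731 per arm, or 731 − 520 = 211 more in each arm carried to the end, so the stated power or the sample size must be restated. That value is more than sufficient if only one arm is kept (two-sided error 1.2% to 1.9% in the best-of-six case), so a value matched to the final selection rule could cost less. Dunnett is one option, suited to HCQ as sole reference. The protocol speaks only of comparisons between groups, so the reference should be settled first.
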